### 2.4. Measurements

Dynamic pedography will be used for gait analysis to assess static and dynamic plantar pressure and changes that occur before and after completion of the exercise program and after using the customized insoles. A myotonometer will be used for muscle properties assessment. Muscle strength will be tested with a digital handheld dynamometer. The contralateral non-injured ankle will serve as a control.

#### 2.4.1. Gait Analysis

During gait analysis, the patient will be asked to stand upright on the Scheinworks treadmill (Model FDM-TDSL-3i). Initially, a static measurement of plantar pressure will be taken. Before starting their treadmill exercise, the participants will receive a safety briefing and a 3 min familiarization period for walking. Then, patient will begin walking on the treadmill while dynamic measurements are recorded. The treadmill features a plantar pressure measuring plate integrated underneath it, which has capacitive sensors to measure the distribution of plantar pressure not only during orthostasis but also during walking. The sensor plate integrated into the treadmill offers analysis of the pressure, power, time, and step parameters and evaluation of gait symmetry as standard [12,35,40]. The pressure plate has a sensing area of 94.8 × 40.6 cm and incorporates 5376 capacitive sensors, with a resolution of 1.4 sensors/cm^2^, a measurement area of 1–120 N/cm^2^, and precision of ±5% of the final value. The treadmill has a contact surface of 200 × 92 cm and its belt speed can be adjusted between 0.2 and 24 km/h in 0.1 km/h steps [35]. Before the baseline assessment, the patients will be given a trial using the platform to become familiar with the test method. During this examination, the participants will walk barefoot, while the platform will be calibrated before each attempt. Each patient will be asked to perform five trials, out of which the average of three good attempts for each evaluated parameter will be considered for analysis. A good attempt is defined as both feet making contact with the platform at least three times during walking, eyes remaining open throughout the test, walking without stopping at the participant’s preferred speed, and an absence of excessive trunk rotation [12,40,41].

During these analyses, the data interpretation will occur directly after the measurement. The software will be used to calculate spatial and temporal gait parameters and to analyze the data. The results will then be immediately available in the form of a report.

#### 2.4.2. Myotonometric Evaluation

The Myoton PRO Digital Palpation Device with Software v.5.0.0.232 is used for myotonometric assessment [42]. This evaluation takes five minutes per test procedure, which will be conducted in two rounds. The patients will be tested for leg muscles in different compartments while in a supine or seated position for the anterior and lateral compartment and in a relaxed prone position for the posterior compartment. Only the superficial muscles of the leg will be assessed using the myotonometer. The tibialis anterior muscle will be tested in the anterior compartment (Figure 2a). The gastrocnemius muscle will be tested in the posterior compartment of the lower leg (Figure 2b). The peroneus longus muscle will be assessed in the lateral compartment. Similar to previous studies, the medial and lateral gastrocnemius muscles will be measured at one-third distal to the lower leg length in line with the popliteal crease to the malleolus [43], the peroneus longus muscle will be measured at a proximal one-third from the head of the fibula to the lateral malleolus [44]. The tibialis anterior muscle will be measured at one-third of the distance between the tibial tuberosity and the lateral malleolus. The muscle belly (lateral to this line) will be palpated during gentle resisted isometric contraction (ankle dorsiflexion) [45].

The myotonometric assessment will be performed for both the affected and non-affected lower extremities. The device records the natural damped oscillation of the soft tissue as an acceleration signal and calculates it with an external mechanical impulse with low force, rapid release, and constant preload. MyotonPRO technology provides an assessment of muscle tone, elasticity, dynamic stiffness, tension state, relaxation time, and relaxation time strain ratio of the targeted muscle [42,46].

#### 2.4.3. Muscle Strength Evaluation

For muscle strength testing, a MicroFET2 dynamometer (Hoggan Scientific, Salt Lake City, UT, USA) will be used. The microFET2 Digital Handheld Dynamometer muscle tester is a portable and accurate device that is specifically designed for taking objective, reliable, and quantifiable muscle testing measurements [47]. Hand-held dynamometry is a commonly used method for measuring ankle plantarflexion strength. It has been shown to be a valid, sensitive, and reliable measure of foot and ankle strength. However, the reliability of assessing ankle plantarflexion strength can vary, especially with higher plantarflexion forces [48]. Fixed dynamometers are suggested to improve reliability and are considered the gold standard for measuring both isokinetic and isometric strength [49]. Nonetheless, their high cost and lack of portability can make them less practical for clinical settings. In their study, Davis et al. [48] concluded that both methods of measuring ankle plantar–flexion force are reliable. Hand-held dynamometry alone is more consistent between repeated measures and might be more precise in detecting true change. On the other hand, fixed dynamometers might be more accurate, especially among stronger individuals. In our study, participants will be barefoot and will perform ankle plantar flexion and dorsiflexion while lying supine with their ankles in plantar grade, with their hips and knees extended. The dynamometer will be placed over the metatarsal heads on the sole of the foot for plantar flexion, and on the dorsum for dorsiflexion, and the examiner will apply unmoving resistance during 3 s contractions (Figure 3). For extra stability during ankle plantar flexion assessment, the dynamometer will be positioned against a heavy wooden block. We will repeat both muscle testing procedures for three trials, with a 5 s rest between them. The analysis will consider the mean of the three trials [46]. The muscle strength evaluation will be performed for both affected and non-affected lower extremities.

#### 2.4.4. K-Force Plate

K-Force plates are a dependable option for examining both static and dynamic balance across a variety of movements such as standing, squatting, and counter-movement jumps [50]. These plates measure both the center of pressure and weight distribution, allowing for an objective assessment of balance (Figure 4) [51,52].

During evaluation, participants will be asked to perform a single-leg balance test under two different conditions. The first condition will involve standing on both the fractured and healthy leg for three repetitions, with open eyes, on the K-Force Plates. The second condition will involve standing on both legs again for three repetitions, this time with eyes closed on the K-Force plates [50,51].

In the single-leg balance test, participants have to stand on one leg for 10 s while focusing on a point 5 m away, with their hands on their hips and the non-load-bearing leg slightly bent at the hip and knee. The test duration of 10 s was chosen based on the time norms of the closed-eye condition during a unipodal balance exercise [51].

## 3. Expected Results

After the first assessment, we anticipate weaker results for the affected leg in terms of myotonometric parameters and muscle strength when compared to the non-affected leg. We believe that the four ankle muscles (anterior tibialis, medial and lateral gastrocnemius, and longus peroneus) on the injured side will display increased frequency and dynamic stiffness, as well as reduced elasticity and a lower relaxation to deformation time ratio. As for isometric muscle force, we expect the ankle dorsiflexors, plantar flexors, and peroneal muscles on the affected limb to exhibit lower values than those of the healthy limb. However, after three months of participating in a physical exercise program, with or without the use of foot orthosis, we predict that there will be no significant differences in myotonometric parameters and muscle strength between the injured and non-injured lower extremity.

Initially, it is likely that there will be a difference in balance while standing on one leg with eyes open between the affected and non-affected limb. However, we anticipate that this discrepancy will decrease significantly within the 3-month exercise program. Additionally, participating in a physical exercise program, with or without a foot orthosis, is expected to improve balance during standing with both conditions of eyes open and eyes closed compared to the first assessment.

At this point, we are not able to make any assumptions about which group—the one using customized foot orthoses and undergoing physical exercise program or the one solely completing the physical exercise program—will have better results regarding myotonometry, muscle strength, and balance.

## 4. Discussion

To date, this will be the first study to assess both the properties of ankle muscles and foot kinematics after tibial pilon fracture surgery. The study will be a randomized one, analyzing the differences between the patients that will follow a 3-month physical exercise program and will also wear customized foot orthoses versus patients that will attend only rehabilitation. The assessment involves four different testing procedures: myotonometry, muscle strength testing, gait analysis, and double-leg and single-leg balance tests.

Myotonometry measures the state of tension (when the muscle is relaxed), biomechanical properties (dynamic stiffness and logarithmic decrement, characterizing elasticity or dissipation of natural oscillation), and viscoelastic properties (mechanical stress relaxation time and the ratio of relaxation time to deformation time, characterizing creep) [42]. Anterior tibialis, medial and lateral gastrocnemius, and longus peroneus will be tested through myotonometry. The anterior tibialis muscle is responsible for ankle dorsiflexion and assists in foot inversion. The longus peroneus muscle’s main action is foot eversion and assists in ankle plantar flexion. Gastrocnemius muscles and the soleus muscle are responsible for ankle plantar flexion. We decided not to test the soleus using myotonometry as it is a more profound muscle [53].

The isometric muscle force of ankle dorsiflexors, plantar flexors, and peroneal muscles will be measured using a hand-held dynamometer [47,48]. We chose to apply dynamometry for these muscles (as a group muscle testing) due to the anatomical and biomechanical features.

The muscles of the lower leg produce different movements in the ankle and foot that are crucial for daily activities such as walking and running. While the individual muscles in each compartment have additional functions, it is important to consider muscle groups as a functional unit. The anterior or dorsiflexor compartment, that contains the tibialis anterior, extensor digitorum longus, fibularis tertius, and extensor hallucis longus mainly produces dorsiflexion of the foot at the ankle joint (an action particularly important for the swing phase of the gait cycle in which the leg is lifted off from the ground). The posterior or plantar flexor group, which consists of a superficial layer comprised of the gastrocnemius, plantaris, and soleus, and a deep layer comprised of tibialis posterior, flexor hallucis longus, popliteus, and flexor digitorum longus muscles, primarily produces plantar flexion of the foot at the ankle joint (an action important for the toe-off phase of the gait cycle, in which the foot prepares to leave the ground). The lateral or fibular group, which consists of fibularis longus and fibularis brevis, mainly produces an eversion of the foot at the subtalar joint. This action plays an important role in maintaining balance while standing on one leg or walking on rough surfaces [53].

Except for the assessment of ankle muscle properties and muscle strength, our study aims to analyze balance and gait. K-Force plates measure the static and dynamic balance in a wide range of conditions (stance, squats) [50]. In the current study, the patients’ balance will be tested during standing (eyes open, eyes closed) and during single-leg standing tests (eyes open). Previous studies have shown that reduced ankle dorsiflexion range of motion is often linked to poor balance and associated activities in ankle fracture patients [19,20]. This connection is supported by research conducted on healthy individuals as well as those with chronic ankle instability, where reduced ankle dorsiflexion range of motion has been found to alter lower limb kinematics and reduce balance, particularly during dynamic actions in the sagittal plane such as single-leg reaching or landing tasks [54].

The use of treadmills with pressure platforms as outcome assessment tools is becoming more common in clinical and research settings. However, there is limited published evidence on the effectiveness of these systems. These treadmills capture electronic footprints which allow for quick measurement of basic gait parameters and the vertical component of ground reaction force over many steps. They have been used to monitor gait patterns in patients with musculoskeletal and neurological disorders [55,56]. Normal gait requires sufficient muscle strength, balance, proprioception, joint mobility, and no pain. Gait analysis is used to measure the effectiveness of a certain therapy by comparing patients’ gait parameters to those of healthy individuals. It enables the assessment of functional outcomes, rehabilitation effectiveness following surgical treatment for musculoskeletal injuries, and individualized treatment and rehabilitation programs [22,23,24,25,26,27]. Restoring gait function comparable to healthy subjects is crucial for patients’ quality of life [19,20,21,57].

Our study will include patients with pilon fractures that have been treated surgically. For the management of these fractures, the most common approach is open reduction and internal fixation with plates and screws. External fixation devices are very useful in fractures with associated soft tissue damage and are used as a temporary reduction and fixation method until osteosynthesis with plates and screws is permitted by the soft tissue appearance or biological status of the patient. External fixation devices can be used in certain cases as a definitive treatment method. A study conducted by Wyrsch et al. [58] compared the effectiveness of open reduction and internal fixation with external fixation as a definitive treatment. Their study revealed that postoperative infections were significantly more common among patients who underwent open reduction and plating. However, there were no statistically significant differences in functional outcomes and complications between the two treatment options. In a meta-analysis by Wang et al. [59], that included nine studies with 498 fractures, no significant differences were found between open reduction and internal fixation, and limited internal fixation combined with external fixation in terms of absence of healing, vicious or delayed healing, superficial and deep infections, arthrosis symptoms, or chronic osteomyelitis.

Tibial pilon fractures often result in complications leading to gait impairment. The lack of improvement in joint mobility results in modified gait parameters. Limited movement in the ankle joint can increase energy expenditure while walking and lead to poorer gait parameters [41]. Pawik et al. [60] observed symmetry in the gait parameters after treating pilon fractures with the Ilizarov external fixator. This method of stabilization allows the restoration of gait parameters with differences from those observed in healthy subjects. In particular, the biomechanics of the lower limbs remain disturbed. The study of Wietecki et al. [16] assessed the kinematic gait parameters in 23 patients with pilon fractures treated with the Ilizarov method. The surgery was performed 24–48 months prior to study measurements. The authors recorded significant limited ankle dorsiflexion, inversion, and abduction of the operated leg in comparison to the non-operated one. They suggested the need for intensive ankle joint rehabilitation following pilon fracture treatment. Houben et al. [13] also stated that patients with pilon fractures showed altered gait compared to healthy controls. There was lower speed and less range of motion between the hindfoot and tibia in the flexion/extension and inversion/eversion, but more range of motion in the abduction/adduction during the push-off phase. The type of fracture was significantly correlated to the passive range of motion.

Patients with tibial pilon fractures usually experience complications in the muscles of the affected limb, leading to gait alteration and difficulties in daily activities. Prolonged rest or immobilization can worsen these complications. Morasiewicz et al. [41] indicated that increased tension in the postural muscles and the higher energy demand related to the shortening and deformation of limbs worsens the parameters of the gait and disturbs its symmetry. The disturbed phase of propulsion may result from the weakening of the gastrocnemius muscle [41]. Aiona et al. [61] reported that shortening of the limbs causes pain and the activation of compensatory mechanisms, which causes higher energy expenditure and affects gait parameters.

To our knowledge, the current study is the first to assess the myotonometric properties of four muscles (anterior tibialis, medial and lateral gastrocnemius, and longus peroneus) in patients after pilon fracture. The study of Halvachizadeh et al. [7] assessed the degree of soft tissue involvement following closed ankle and pilon fractures. Analyzing the mechanical characteristics, the authors noted that the local tension of the soft tissue was affected by the injury; the local frequency and local stiffness were increased, while the stress/relaxation time decreased. In contrast to this study which assessed using myotonometry the soft tissue (soft spot between the lateral malleolus and Achilles tendon), our study will evaluate the muscle myotonometric properties.

Attempting to improve foot and gait biomechanics through the use of orthotics is a commonly used practice for various neurological and musculoskeletal conditions. In the study of Lee et al. [30], they compared the static balance effects of bare foot and ankle–foot orthoses in patients with stroke with foot drop. The measurements showed a significant increase in static balance with the use of orthoses. A study conducted by Quacinella et al. [15] used a dynamic exoskeletal orthosis designed to improve gait for patients experiencing functional loss after a high-energy tibial pilon fracture. The study evaluated various gait parameters such as velocity, cadence, stride length, and single-leg stance. The results showed that only gait velocity improved following the application of the orthosis, while the other gait variables remained unchanged [15,31].

In our study, all patients (group with or without foot orthosis) will attend a 3-month physical exercise program. We anticipate that most of the patients involved will take part in the study between 6 months and 1 year after surgery.

## 5. Conclusions

The randomized controlled study aims to provide options for the long-term management of treatment for patients that have followed surgery for tibial pilon fractures. After 3 months, the assessments will record which of the two therapeutic alternatives (physical exercise program with or without wearing customized foot orthoses) achieves better outcomes in what concern the regain of ankle muscle properties and tone, as well as the restoration of gait and balance.

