
### Study Objectives

This study aims to conduct a comprehensive assessment of the muscles and gait parameters in patients who have undergone surgery for pilon fractures and compare the results before and after a physical exercise training program with or without wearing foot orthoses represented by customized orthotic arch support insoles. The purpose of our study is to investigate whether combining foot orthoses with an exercise program leads to improved gait parameters, balance, and ankle muscle properties compared to the exercise program alone.

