### 2.1. Sample Size Calculation

The sample size was calculated using G*Power 3.1.9.7 (Heinrich-Heine-Universität, Düsseldorf, Germany), with a significance level of 0.05, 0.8 power, and an effect size of 0.8. A total of 42 subjects will participate in the study (21 per group) [33].

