#### 2.2.4. Interventions

Before the baseline assessment, patients will be divided into two groups. Both groups will undergo an identical exercise program. Group 1 will also wear carbon foot orthoses with full reinforcement specially designed to correct the asymmetries detected on the first set of measurements. Gait parameters analysis can help determine specific movement asymmetries [12,13,14]. The Scheinworks treadmill will be used for this purpose, allowing a practical equilateral overview of important gait parameters [35]. During the analysis, the following parameters were taken into consideration: maximum force exerted by the forefoot and backfoot (expressed as a percentage in relation to body weight); step length (measured in centimeters), which is the distance between the foot contacts on opposite sides of the body; stance phase (expressed as a percentage), which is the period of the gait cycle when the foot is in contact with the ground; swing phase (also expressed as a percentage), which is the period of the gait cycle when the foot is not in contact with the ground; step time (measured in seconds), which is the time between the heel contact of one side of the body and the heel contact of the opposite side; stride time (measured in seconds), which is the time taken for the left and right limbs to complete one stride; step cadence which is the number of steps taken per minute, and velocity (measured in kilometers per hour), which is the speed of gait [12,16,35]. A blueprint or scan of the feet will also be performed. Having determined the correct shoe size, a trial insole will be made to fit the diagnosis. Further corrections can be made if the desired gait pattern has not yet been achieved. In most cases, the insole’s influence should be directly recognizable after a couple of steps. The insoles will be designed for both injured and non-injured side based on patients’ specific needs. The movement cycles can be recorded with patients going barefoot, wearing shoes, or foot orthoses [36]. The carbon element that stiffens the orthosis is narrow, while the cover is wide, allowing for optimal fitting in various shoes without causing damage to the carbon [35], so that patients can wear them every day regardless of the type of footwear used and the type of activity undertaken.

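### The article promises a verdict on which treatment does better across four domains, but names no primary outcome and does not say which outcome the effect size of 0.8 refers to

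*Protocol article*

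**What the plan says.** The Study Objectives ask whether adding orthoses to exercise "leads to improved gait parameters, balance, and ankle muscle properties compared to the exercise program alone". The Conclusions turn this into a single comparative verdict: "the assessments will record which of the two therapeutic alternatives (physical exercise program with or without wearing customized foot orthoses) achieves better outcomes". The Abstract says the same. Neither these sections nor Measurements, Expected Results or Discussion ranks one domain or parameter above another.

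Section 2.1 sizes the trial "with a significance level of 0.05, 0.8 power, and an effect size of 0.8", giving 42 patients, 21 per group. It cites a source but states no outcome, standard deviation, difference, test or sidedness.

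The parameters are spread over several sections:
- **Myotonometry.** Section 2.4.2 describes "assessment of muscle tone, elasticity, dynamic stiffness, tension state, relaxation time, and relaxation time strain ratio of the targeted muscle", six items. The Discussion lists five and Expected Results four. Four muscles are tested.
- **Strength.** The Discussion names three muscle groups. Section 2.4.3 describes the procedure for two movements.
- **Gait.** Section 2.2.4 says that "the following parameters were taken into consideration: maximum force exerted by the forefoot and backfoot", then adds step length, stance, swing, step time, stride time, cadence and velocity, nine in all.
- **Balance.** The Discussion gives three conditions. Section 2.4.4 adds single-leg standing with eyes closed, making four.

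Expected Results declines to predict which group will do better on myotonometry, strength or balance.

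**The concern.** A comparative verdict needs a rule for reaching it. Here any of several dozen between-group differences could be cited in support of either arm, and the article does not say what follows if the arms do better on different parameters. Because Expected Results makes no prediction for three of the four domains, such a split is a real possibility.

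The sample size does not settle the matter. An effect size of 0.8 is a standardised difference, and without a named outcome the reader cannot judge whether it is plausible or worthwhile.

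Redundancy adds to the problem. By the definitions in section 2.2.4, stance and swing percentages sum to 100, and cadence in steps per minute is 60 divided by mean step time in seconds. One gait difference could therefore be reported as two pieces of evidence.

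**Working it through.** **1. The plan's own sample size.** Inputs from section 2.1: alpha 0.05, power 0.8, effect size 0.8 (read as Cohen's d), 21 per group. Method: two-sample t test, noncentral t distribution, df = 2 × 21 − 2 = 40, noncentrality = 0.8 × √(21/2) = 2.59.

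| Test | Power at 21 per group | n per group for 80% power |
|---|---|---|
| One-sided 0.05 | 81.7% | 21 |
| Two-sided 0.05 | 71.6% | 26 |

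The stated 21 per group is reproduced only with a one-sided test.

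**2. The number of parameters**, counted on one leg at 3 months.

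| Domain | Shortest list | Middle | Longest list |
|---|---|---|---|
| Myotonometry (items × 4 muscles) | 4 × 4 = 16 | 5 × 4 = 20 | 6 × 4 = 24 |
| Strength | 2 | 3 | 3 |
| Gait | 9 | 9 | 9 |
| Balance | 3 | 3 | 4 |
| Total | 30 | 35 | 40 |

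The count is an inference from the lists. The nine gait parameters appear under Interventions, where they serve the insole design. The gait outcome section (2.4.1) refers only to spatial and temporal parameters in general.

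**3. Chance of at least one false positive.** Assumptions, none of them stated in the article: no true effect on any parameter, each tested unadjusted at two-sided 0.05, and any single result able to support the conclusion.

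If independent, the chance is 1 − 0.95^k:
- k = 30: 78.5%
- k = 35: 83.4%
- k = 40: 87.1%

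For a common correlation ρ, write each test statistic as √ρ·U + √(1−ρ)·e, with U shared by all tests and e separate for each. The chance is then 1 − E[{Φ((1.96 − √ρU)/√(1−ρ)) − Φ((−1.96 − √ρU)/√(1−ρ))}^35].

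| Common correlation (assumed) | 35 tests |
|---|---|
| 0 | 83% |
| 0.3 | 71% |
| 0.5 | 54% |
| 0.7 | 36% |
| 0.9 | 18% |

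Simulated t tests with 21 per arm agree within about two percentage points. If correlation is instead clustered (each muscle's myotonometry, strength, gait and balance as separate clusters), with assumed within/between values of 0.5/0.2, 0.7/0.3 and 0.8/0.5, the simulated chances are 72%, 61% and 46%.

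The expected number of false positives is 35 × 0.05 = 1.75, whatever the correlation.

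**4. Effect of the redundant pairs.** Removing swing percentage and cadence leaves 33 tests: 1 − 0.95^33 = 81.6% if independent. Dropping them stops double counting but does not solve the multiplicity.

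**The case against.** Several stronger readings are tempting, and the documents do not support them.

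- **That the effect size belongs to no outcome.** Section 2.1 cites a source that is not shown and might identify one. What can be said is that the article does not state the outcome.
- **That 35 parameters is a minimum.** Expected Results names four myotonometric items and section 2.4.3 describes two strength movements, so the shortest lists give 30. A range of roughly 30 to 40 is what the text supports.
- **That a chance winner is likely.** The article says the assessments will record which alternative does better. It does not say that one p value below 0.05 will decide. The analysis plan is not shown and may adjust for multiplicity. The figures also depend on correlation: for 35 tests the chance falls below 50% once the common correlation is above about 0.5. High correlation is plausible within myotonometry, where all values for a muscle come from one oscillation signal, and among gait parameters that are functions of each other.
- **That the sample size is meaningless.** For any single outcome with a true standardised difference of 0.8, 21 per group gives the power shown in the working.

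These points limit the magnitude. They do not supply a primary outcome. A protocol article may leave multiplicity adjustment to an analysis plan, but it does not commonly leave its primary outcome there. The registry entry mentioned in section 2.2 is not shown and may name one. If so, the article disagrees with it by silence.

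**Conclusion.** The point stands in limited form. The article commits to a verdict across four domains, names no primary outcome, and does not tie the 0.8 in section 2.1 to any outcome. Followed as written, it lets any of roughly 30 to 40 comparisons, some redundant by definition, support the headline conclusion.

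The size of the risk is conditional on unadjusted testing with any result counting. On that basis it runs from 83% under independence to 18% at a common correlation of 0.9, against a nominal 5%. The documents give no correlations, so no single figure in that range can be preferred. That the gap matters does not depend on which figure applies, because even the lowest is more than three times the nominal level.

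**What to change.** Before any between-group analysis:

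1. Name one primary outcome at 3 months and justify it. Gait velocity, listed in section 2.2.4, is one candidate. The Discussion reports that it improved with an orthosis after pilon fracture, but that was a dynamic exoskeletal device, whereas this trial uses insoles and tests gait barefoot on a treadmill. The choice is the investigators'.
2. Base the conclusion about which treatment does better on that between-group comparison.
3. Label all other parameters secondary or exploratory, and do not present swing percentage or cadence as evidence separate from stance percentage and step time. If confirmatory claims are wanted from several domains, adjusting only within each of the four is not enough: at 5% per domain the overall error is 1 − 0.95^4 = 18.5% if the domains are independent.
4. In section 2.1, state the outcome to which 0.8 applies and the sidedness, and restate the power for 21 per group accordingly.
5. If the registry entry already names a primary outcome, align the article with it. If not, update the entry.

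The drafting cost is small. The real costs are that fewer parameters can support a confirmatory claim, and that the stated power becomes less favourable if the test is two-sided: restoring 80% would take 26 per group, 52 patients rather than 42. Keeping all 35 parameters confirmatory would cost more. A two-sided Bonferroni adjustment leaves 22.4% power per outcome at 21 per group and needs 54 per group for 80%.
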